## Abstract

**Background:** Decades of research, largely from associational studies, show that the relationships of movement proficiency with the cognitive and social aspects of development are particularly strong in early childhood. Children who move proficiently tend to have better cognitive skills and social behaviors. However, the mechanisms that underpin these relationships remain unclear and research that explores causation is necessary. This study will explore the antecedent role of movement proficiency in the cognitive and social domains of child development, by examining whether a targeted movement skills training program facilitates improvements in cognitive and social skills.

**Methods:** A group-randomized controlled trial will be conducted, implementing a fundamental movement skills training program in Hong Kong kindergartens. Participants will consist of children aged 3–5 years (*N* = 158) who will be randomly allocated by class to either a training or active control condition. The training program (10 weeks × 2 bouts) will be informed by an error-reduced approach to skills learning, which will involve careful design and manipulation of equipment and training environment to minimize practice errors. The active control condition will consist of typical movement activities implemented in the kindergartens in the context of the local curriculum guide. Outcomes will be measured using standardized tests of gross motor skills proficiency, executive functioning, and social skills. Measurements will occur at baseline, mid-training, post-training, and follow-up. Latent variable longitudinal modeling will be used to analyze changes in the outcomes, with covariates that include sex, body composition, fine motor skills, and physical activity.

**Expected Results:** The findings will subsequently be reported consistent with the Consolidated Standards of Reporting Trials (CONSORT) statement. Contributions to knowledge and understanding of child development are expected, through evidence of causal mechanisms surrounding the relationship of motor with cognitive and social development. The findings will also inform policy and practice related to early childhood development and education.

## Introduction

A child who is proficient at moving is enabled to interact with the environment in increasingly complex ways. Early on, Piaget (1963) noted that motor skills influence the number and types of opportunities for children to interact with others. From a dynamic systems perspective (Thelen and Smith 1996; Thelen, 2005), a relatively small change in motor development – enabled by such interactions – can have an escalating impact on social and cognitive functions.

Motor skills are key contributors to children’s ability to play and interact with others, therefore influencing their later social standing with peers. For instance, poor gross motor skills have been related to weakness in emotion comprehension in early childhood (Piek et al., 2008a). Longitudinal studies have also shown that motor skills at the age of five to six years predicted adaptation and social behaviors in school one year later (Bart et al., 2007); motor skills at the age of six to seven years influenced social status among peers at nine to ten years (Ommundsen et al., 2010). This could be related to the observation that social play is reduced and social reticence is heightened in children with poor motor skills (Bar-Haim and Bart, 2006). Early peer acceptance is also known to be related to adult adjustment (Bagwell et al., 1998) and later academic achievement (Wentzel and Caldwell, 1997), suggesting that there may be long-term consequences to the risks that poor motor skills in early childhood pose on psychosocial development. This highlights the importance of investing in motor skills development in early childhood to mitigate future wellbeing problems.

Gross motor skills in early childhood have also been shown to be associated with cognitive development (Veldman et al., 2019) and to predict levels of cognitive processing later in life (Murray et al., 2006; Piek et al., 2008b). From longitudinal studies, early gross motor skills have been shown to predict cognitive efficiency (Lopes et al., 2013; Haapala et al., 2014) and academic achievement in subsequent school transition (Niederer et al., 2011; Roebers et al., 2014). A review of intervention programs suggested that increasing the amount of physical and movement activities might generate improvements in executive functioning of school-aged children (Diamond and Ling, 2016). However, the mechanisms through which movement-based interventions can improve executive function have yet to be fully understood.

Executive function is an umbrella term that refers to a set of higher order cognitive processes (e.g., inhibitory control, working memory, and cognitive flexibility) that are associated with the prefrontal cortex area of the brain (Hughes and Ensor, 2011). Core components of executive function develop during early childhood, forming a critical foundation for subsequent development of cognitive processes in adulthood (Garon et al., 2008). McClelland and Cameron (2019) highlighted that both executive function and motor skills are foundational skills that should be nurtured during early childhood. The years from three to five make up an important period in the development of executive function (Garon et al., 2008) and would presumably be the ideal age to examine whether they can be enhanced alongside motor enrichment.

The relationship between motor skills and other developmental domains appears to be strongest during the early years of life (Libertus and Hauf, 2017). This suggests that a robust foundation of movement proficiency in early childhood may be a critical antecedent to the development of other domains. However, the state of evidence, as discussed above, has been largely drawn from associational studies; there is a knowledge gap that limits our understanding of the mechanisms through which the movement proficiency influences the other domains of child development. Experimental designs are needed to reveal the underlying mechanisms or processes that drive development and establish causal relationships (Getchell et al., 2020).

Previous experimental studies that examined the impact of movement-focused programs on other developmental domains have tended to focus on primary school-aged children. For instance, a group-randomized physical education intervention involved children aged 5 to 10 years (Pesce et al., 2016). Improved motor coordination was accompanied by gains in executive functioning and attention, but only when children engaged in physical activity on their own. In contrast, an after-school program for early primary school children that trained fundamental movement skills did not yield significant benefits in cognitive functions (Lee et al., 2020). It was noted that the sample size of this other study was relatively small, and cognitive functioning was measured with a parent-proxy report.

There have been relatively limited intervention studies in pre-primary school-aged children. One such study in South Africa found that a community-based movement program was beneficial for both gross motor skills and cognitive functioning among children aged three to six years from disadvantaged communities (Draper et al., 2012). The researchers speculated that improvements in both cognitive functioning and gross motor skills could simply be attributed to the general stimulation afforded by participating in the program, considering the general lack of space and resources for activities prior to implementation of the program. The extent to which movement training contributed to improvements in cognitive functioning remained unclear, and the mechanisms that facilitated the improved motor skills and cognitive functioning were unexplored. It is therefore necessary that experimental studies that implement movement skills training are conducted in which mechanisms and interacting factors can be examined (Getchell et al., 2020).

### Movement Skills Training of Children

Skills, such as locomotor and object manipulation, are not acquired innately as children grow up (Clark, 2005). Instead, planned programs are needed to facilitate the skills acquisition during early childhood (Logan et al., 2012). How should movement skills be trained in early childhood? Masters et al. (2013) suggested that the stage learning models of motor skill acquisition (Fitts and Posner, 1967) seem inappropriate during early childhood. Stage models suggest that a learner goes through an initial cognitive stage when learning motor skills during which methods to perform movements successfully are formulated, and the validity of perceived feedback is judged. In this stage, there is heavy reliance on cognitive resources and language ability to process and formulate rules and methods for movement performance; cognitive and verbal engagement is reduced later after extensive practice. Considering that cognitive resources and language skills are not fully developed in early childhood, it is unlikely that initiating a cognitive stage of skill learning as described above would be ideal for children at this stage.

In training motor skills during early childhood, it is therefore necessary to consider that skills may be best acquired through less engagement of verbal processes (e.g., instructions and rules). Masters and colleagues have developed this approach under the label of implicit motor learning (Masters, 1992; see Masters et al., 2019, for a recent review). Neurocognitive research has shown that young children tend to rely more on visual codes and less on verbal labels (Alloway et al., 2006) and rely less on executive resources when performing dual tasks compared to older children (Ang and Lee, 2010). Grounded on this evidence, an approach to training motor skills wherein practice errors are minimized may be suitable during early childhood.

When learners commit practice errors, they seek alternative movement solutions, form rules to support successful performance, and consequently draw upon their working memory resources (Maxwell et al., 2001). On the contrary, when practice errors are minimized, motor skills are learnt with less reliance on cognitive resources, which is suitable for children whose cognitive functions are still developing (Capio et al., 2012). This is the basis of the error-reduced approach, which has been shown to improve gross motor skills proficiency of children without dependence on short-term memory capacity (Capio and Eguia, 2020).

In earlier work, the error-reduced approach was tested specifically in the training of overhand throwing by children (Capio et al., 2013a). Practice errors were limited in the initial stage of learning by incrementally manipulating task difficulty (i.e., throwing at targets that were large enough to ensure high success rates). Movement performance was found to improve; children displayed the ability to engage in a secondary cognitive task (i.e., counting backward) without it disrupting movement performance. This suggested that movement performance was not dependent on cognitive resources. The findings were replicated in children with cognitive limitations (Capio et al., 2013b), providing further evidence that this approach is relatively less reliant on cognitive resources. Interestingly, children who trained with an error-reduced approach manifested a greater increase in spontaneous throwing activity during free play. Capio et al. (2013b) suggested that greater experiences of success during practice facilitated subsequent sustained engagement and motivation; these two factors have been shown to mediate the positive effect of movement training on cognitive development (Pesce et al., 2016). As such, the error-reduced training could be an approach that not only improves movement performance but also aids cognitive development. Greater experience of success during practice has been associated with enhanced self-efficacy (Muller and Roder, 2010), which suggests that it could contribute to psychosocial development in early childhood. While converging evidence from studies involving children of different abilities (i.e., Maxwell et al., 2017; Capio et al., 2018) has indicated the value of an error-reduced approach to motor skills training, the potential effects on cognitive and social development have yet to be verified.

### Research Gap and the Present Study

It is evident that movement skills proficiency plays a crucial role in optimal cognitive and social development in early childhood. Children who have proficient motor skills tend to have positive outcomes in a number of child development domains. The evidence to date, however, has been largely drawn from studies of association, and the mechanisms underlying the apparent relationships between the motor domain and other domains of development continues to be poorly understood (Libertus and Hauf, 2017). With limited evidence from intervention studies, the antecedent role of movement proficiency in child development is an area that needs further exploration. It remains unclear whether enhanced movement proficiency can directly impact cognitive and social development in early childhood, or whether all developmental domains are similarly influenced by factors, such as general stimulation or the early childhood education environment.

From a theoretical perspective, it has been noted that motor development has been relatively neglected when trying to understand childhood behaviors (Rosenbaum, 2005; Iverson, 2010), even though movement enables exploration and expression. This may be due in part to limited evidence from robust experimental designs, which this present study aims to address. The aim of this study is to examine whether improved movement proficiency leads to benefits in the cognitive and social domains of child development. A fundamental movement skill training program, using the error-reduced learning approach, will be implemented and compared with typical kindergarten activities (i.e., active control). It is hypothesized that significant and meaningful improvements will be observed in gross motor skills proficiency from baseline to immediate and delayed time points following training; improvements will be greater among those in an error-reduced condition compared to those in the active control group. It is further hypothesized that improvements will be found in executive functioning and social competence from baseline to immediate and delayed time points following training; improvements will be greater for those who displayed larger gains in gross motor skills proficiency. Executive functions will be based on standardized tests of inhibitory control and working memory, while social competence will be based on standardized reports by teachers. Factors that could influence the main variables of interest will be accounted for.

## Materials and Methods

### Context and Design

The study will be implemented in Hong Kong, where children aged three to five years attend kindergarten classes. All local kindergartens follow the same curriculum which stipulates a learning area of physical fitness and health, inclusive of fundamental movement skills development (Curriculum Development Council, 2017). This is a two-arm (training vs. active control), group-randomized intervention study that is situated in the kindergarten setting; the intervention will be delivered in partnership with teachers.

### Participants

A purposive sampling approach will be taken with the following inclusion criteria for participants: Children (1) aged three to five years, (2) enrolled in a local kindergarten within the same territory as the research center (i.e., New Territories and Hong Kong), and (3) have no diagnosed neurodevelopmental, medical, or orthopedic condition that is contraindicated to moderate intensity physical activity or that requires special educational needs support. In previous research, a six-week gross motor skills training program led to improved motor proficiency, with effect sizes ranging from 0.28 to 0.45 (Brian and Taunton, 2018). Taking a conservative approach, it was calculated that to achieve 80% power (two-tailed alpha at 0.05), with an effect size of 0.28, and accounting for between-group and within-group interactions, a total sample of 144 is required to compare two groups (i.e., training and control) at four testing points. Accounting for 10% potential attrition rate, 79 participants per group (*N* = 158) will be recruited. The participants will be randomly allocated as a group (i.e., one intact kindergarten class) to either training or active control. Typical kindergarten classes in Hong Kong have about 20 to 30 pupils; hence, three to four classes will be allocated to each group (i.e., training and active control). To control for a cluster effect and socioeconomic status being a potential confounder, we had recruited a local kindergarten with at least eight kindergarten classes from a middle-class area.

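### The 80% power stated for 144 children makes no allowance for randomising three to four intact classes per arm, and using one kindergarten does not supply it.

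*Protocol article*

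**What the plan says.** The sample size is set out in one paragraph of the Participants section. A previous six-week motor skills programme is cited "with effect sizes ranging from 0.28 to 0.45". From the lower end of that range, "it was calculated that to achieve 80% power (two-tailed alpha at 0.05), with an effect size of 0.28", and "accounting for between-group and within-group interactions", the article concludes that "a total sample of 144 is required to compare two groups (i.e., training and control) at four testing points". Attrition is then added: "Accounting for 10% potential attrition rate, 79 participants per group", 158 in all.

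The unit of allocation comes only after this: "The participants will be randomly allocated as a group (i.e., one intact kindergarten class) to either training or active control". Because classes hold about 20 to 30 pupils, "three to four classes will be allocated to each group". The number of classes is thus obtained by dividing the children per arm by class size. It is not an input to the power calculation.

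The paragraph's one remark on clustering is about recruitment: "To control for a cluster effect and socioeconomic status being a potential confounder, we had recruited a local kindergarten", one with at least eight classes.

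The Data Analysis section separately says that variance shared by children in the same class will be corrected for with the complex sampling procedure in Mplus.

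**The concern.** When classes are randomised, the precision of the comparison between arms depends on how alike children in a class are and on how many classes there are. The paragraph names neither an ICC nor a design effect, and it treats the choice of a single kindergarten as the control for clustering. But the randomised cluster is the class, and correlation within a class remains when all classes sit in one kindergarten. The article gives reasons to expect some. Teachers deliver the training, a class moves to harder tasks only when every child in it succeeds, and teachers rate social competence.

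What is at stake is the stated 80%. A reader who relies on it will take the trial to be better able to detect a training effect than it is, and may give a non-significant result more weight than it can bear.

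**Working it through.** **Inputs from the Participants section.** Power 80%, two-sided alpha 0.05, effect size 0.28 (metric not stated), two groups, four time points, N = 144, 10% attrition, three to four classes per arm. Children analysed per class: 144/8 = 18 with four classes per arm, 144/6 = 24 with three.

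**Input not in the document.** The class ICC. A range of 0.01 to 0.10 is assumed, with 0 as a reference. For a group-by-time effect the relevant ICC is that of change.

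**Step 1: reproduce 144.** Noncentral F with λ = N × 0.28² and 3 numerator df. At N = 144, λ = 144 × 0.0784 = 11.29.

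- Repeated-measures MANOVA interaction (denominator df N − 4): power 0.7999 at N = 143 and 0.8030 at N = 144.
- 2 × 4 factorial (denominator df N − 8): power 0.7995 at N = 143 and 0.8027 at N = 144.

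Both give 144 as the smallest N that reaches 80%. Both take children as independent, and neither leaves room for a design effect.

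**Step 2: the attrition uplift.** 144 × 1.10 = 158.4 (144/0.90 would be 160), so the step from 144 to 158 is used up by attrition. Even if no child were lost, 158/144 = 1.097 would offset an ICC of only 0.097/(158/6 − 1) ≈ 0.004 with three classes per arm, or 0.097/(158/8 − 1) ≈ 0.005 with four.

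**Step 3: add the class term.** Design effect DE = 1 + (m − 1) × ICC, and effective N = 144/DE. Two power figures follow:

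- 3-df F test as in Step 1, with λ = (144/DE) × 0.0784 and denominator df kept at 140. This shows the design effect alone.
- A 1-df contrast that would have 80% power under independence, so noncentrality (1.96 + 0.84)/√DE = 2.80/√DE, tested against t on classes minus 2 df (6 or 4). That reference distribution is an assumption.

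| Classes per arm | ICC | DE | Effective N | 3-df F | 1-df, class-level t |
|---|---|---|---|---|---|
| 4 (18 each) | 0 | 1.00 | 144.0 | 80% | 65% |
| 4 | 0.01 | 1.17 | 123.1 | 73% | 58% |
| 4 | 0.05 | 1.85 | 77.8 | 51% | 41% |
| 4 | 0.10 | 2.70 | 53.3 | 36% | 30% |
| 3 (24 each) | 0 | 1.00 | 144.0 | 80% | 56% |
| 3 | 0.01 | 1.23 | 117.1 | 71% | 49% |
| 3 | 0.05 | 2.15 | 67.0 | 45% | 31% |
| 3 | 0.10 | 3.30 | 43.6 | 30% | 22% |

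The ICC 0 rows show the cost of having only 6 or 8 classes, before any correlation is assumed.

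**The case against.** The strongest reply is that clustering is not ignored. The Data Analysis section corrects for it at class level, so the single kindergarten is not the only safeguard. That is right about the analysis, and a reader who inferred that the trial will be analysed as if children were individually randomised would be wrong. It does not rescue the power figure, because the correction changes the standard errors and leaves the sample size where it was.

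A second reply is that the size of the loss rests on an ICC the article does not give. This stands. The ICC of change may be smaller than a cross-sectional one, and at 0.001 the design effect alone would leave about 79%. The class-level t figures are also conditional, since the article names the Mplus procedure and no reference distribution.

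Four stronger readings are tempting, and the document does not support them:

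- *The calculation treated the repeated measurements as independent.* The factorial formula would do so, but the MANOVA interaction fits equally well and allows for correlation within a child. The article does not say which was used.
- *The effect size is not conservative.* Read as Cohen's f for two groups, 0.28 would equal a standardised difference of 0.56. But the metric is unstated, and in context conservative means the lower end of the cited range, which is what was taken.
- *The trial has 39% power, or needs some 400 children, before any clustering.* Those figures come from a two-sample test of a standardised difference of 0.28 at one time point. The article plans four time points and growth curves.
- *Separate power is owed for executive function and social competence.* Sizing on the proximal motor outcome is a common choice. The further hypothesis, that larger motor gains go with larger gains elsewhere, is a relation between children to which the between-arm design effect does not directly apply.

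**Conclusion.** The point holds in this form: the 80% is stated for a design with independent children, while the trial randomises six to eight classes. This rests on the exact reproduction of 144 and needs no ICC assumption. The statement that one kindergarten controls the cluster effect is wrong for the cluster that is randomised, and it sits badly with the article's own class-level correction.

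The size of the shortfall is conditional. For an assumed ICC of change of 0.01 to 0.10, the design effect alone gives about 73% to 36% with four classes per arm and 71% to 30% with three. If inference also uses classes minus 2 df, a 1-df contrast has about 58% to 30% or 49% to 22%, and only 65% or 56% at an ICC of 0.

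A reader might infer that the trial cannot detect an effect or must enlarge. The document does not support that. What it shows is that the stated power is unsupported and, for any ICC of 0.01 or more, too high.

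**What to change.** In the Participants section:

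1. Delete the statement that recruiting one kindergarten controls the cluster effect. If wanted, say instead that it removes variation between kindergartens and limits socioeconomic differences.
2. Restate the power, or the minimum detectable effect, for the planned three to four classes per arm. Show the assumed ICC range (for change, if the test is of differential growth), the design effect, and the class-level degrees of freedom.
3. Name the metric of the 0.28, and say that the figure is based on gross motor proficiency.

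The cost is one rewritten paragraph and a less favourable stated power. The correction does not itself call for more children or a change to the planned model.

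### The 10% attrition allowance multiplies by 1.10 instead of dividing by 0.90, so 158 recruited leaves about 142 children, two short of the required 144 (minor)

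*Protocol article*

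**What the plan says.** Everything needed stands in the protocol article, Materials and Methods, Participants.

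- The calculation aims "to achieve 80% power (two-tailed alpha at 0.05), with an effect size of 0.28", and finds that "a total sample of 144 is required to compare two groups (i.e., training and control) at four testing points".
- Recruitment is then set: "Accounting for 10% potential attrition rate, 79 participants per group", a total of 158. The Abstract (Methods) gives the same total.
- On classes: "Typical kindergarten classes in Hong Kong have about 20 to 30 pupils; hence, three to four classes will be allocated to each group". The section adds that the recruited kindergarten has at least eight classes.

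**The concern.** An attrition allowance should leave the required number once the expected loss has occurred. The recruitment figure looks like the required number plus 10% of itself. That is not the same as a number from which 10% can be lost. If so, the trial would miss its own requirement even when attrition is exactly as planned. What is at stake is whether the published sample size meets the 80% power criterion stated beside it.

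**Working it through.** **Inputs (all from Participants).** Required total 144, or 72 per arm; attrition 10%; recruitment 79 per arm, 158 in total; effect size 0.28; two-sided alpha 0.05; power 80%; two groups, four time points.

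**Step 1. Reproduce 144.** The article names neither the metric of the effect size nor the formula. One reading gives 144: the repeated-measures group-by-time interaction in its multivariate form, with 0.28 taken as Cohen's f. Then lambda = N × f² with f² = 0.0784, and the degrees of freedom are 3 and N − 4. The smallest N with power of at least 80% is 144 (lambda = 144 × 0.0784 = 11.29, power 0.803). Other readings do not give it. The univariate interaction test with f = 0.28 and an assumed correlation of 0.5 needs 19 in total. A two-group comparison of means with a standardised difference of 0.28 needs 201 per arm.

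**Step 2. Reproduce 158.**
- 144 × 1.10 = 158.4
- 72 × 1.10 = 79.2, rounded down to 79 per arm, so 158

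**Step 3. Apply the stated loss.**
- 158 × 0.90 = 142.2 in total
- 79 × 0.90 = 71.1 per arm, against 72 required
- The largest loss that still leaves 144 is (158 − 144)/158 = 8.9%, not 10%

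**Step 4. The allowance that works.**
- 144/0.90 = 160
- 72/0.90 = 80 per arm

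**Step 5. Effect on power, on the reading in Step 1.**

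| Evaluable children | Power |
|---|---|
| 142 | 0.797 |
| 144 | 0.803 |

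The difference is about 0.6 percentage points. These figures take the plan's calculation on its own terms, with no term for clustering by class.

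**Step 6. Check the class range.** Counting every pupil as a participant:
- 79/30 = 2.6, so three classes
- 79/20 = 3.95, so four classes

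This is the stated range of three to four. The share of pupils who must enrol to reach 79 is 79/(classes × size):

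| Classes × size | Pupils | Uptake needed |
|---|---|---|
| 3 × 27 | 81 | 98% |
| 3 × 30 | 90 | 88% |
| 4 × 20 | 80 | 99% |
| 4 × 25 | 100 | 79% |
| 4 × 30 | 120 | 66% |

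The article gives no expected uptake.

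**The case against.** The best defence is that the gap does not matter. The 10% is a round planning figure for a potential loss, and actual attrition will very likely miss it by more than two children. A difference of two in 160 is 1.25% and changes no design decision. That stands as an argument about size, and it is why this is a minor point. It does not make the figure right: the required number and the loss rate are both stated, and together they do not give 158.

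A reader might go further and infer that the class plan is impossible, because three classes of 20 to 25 hold only 60 to 75 children and each arm needs 79. The document does not support that. It never says that three classes of that size will supply an arm. The number of classes is derived from the range of class sizes, three going with the larger classes and four with the smaller. Nor does the range permit stopping below 79: the recruitment number is fixed, and eight or more classes allow a fourth in each arm.

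What remains is narrower. Step 6 counts every pupil. Participants sets eligibility criteria, and Ethics and Dissemination requires parental consent and foresees non-consenting children who stay in class without being measured. The range of three to four makes no visible allowance for either.

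**Conclusion.** Wrong as written, but minor. The allowance for 10% attrition was made by multiplying by 1.10 and rounding down. With the plan's own loss rate, 158 leaves about 142 children, two short of the stated 144. This part rests only on figures in the article.

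The power loss of about 0.6 points, from 80.3% to 79.7%, depends on reading 0.28 as Cohen's f in the multivariate interaction test, which the article does not state. On that reading the plan falls just under its own 80% criterion. It is not a material failure of the sample size.

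The class range is consistent with the stated class sizes and is not an error. Its thin margin for ineligible or non-consenting children is an optional point. It depends on uptake, which is not given, and on typical Hong Kong class sizes, since those of the recruited kindergarten are not stated.

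**What to change.** Choose one of two corrections and make the Abstract and Participants agree:

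- set the target at 160 (80 per arm), from 144/0.90; or
- keep 158 as the number recruited and state that about 142 are expected to be evaluable after 10% attrition.

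The first costs two more children, the second one restated sentence.

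Optionally, replace the range of three to four with four classes per arm and state the uptake assumed. The recruited kindergarten already has the eight classes needed. This would also give eight randomised classes rather than the six that three per arm would give. With classes of 20, even four per arm reach 79 only at 99% uptake (79/80), and reach 80 only if every child enrols, so the actual class sizes should be stated too.
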